### Delivery of Lifestyle

Practical issues arise in the delivery of lifestyle interventions in primary care. Previous pilot work by our group has identified contamination of controlled practices could occur, despite using a cluster randomized design. However, this contamination has been small and would favour the null hypothesis. Contaminations can include non-study related public education or public health/physicians targeting dietary and lifestyle interventions that occur as "background noise" intended for use in various clinical settings. We have partnered with local public health and pharmaceutical industry to minimize the impact of these contaminations. Contamination could also arise from patients moving between clinical practices. This will be negligible in the current trial as all clinic staff and patients are rostered to the study practice and cross-coverage between practices is not encountered. These potential contaminants will be discussed during the SNAC and control training sessions for study physicians and staff.

### Timing of the Intervention

Pilot work in our lab has demonstrated that it is impractical to impose strict study start times and recruitment targets within some practices. Hence, there will be no particular matching of start times or recruitment activity between practices. Support will be given to all practices to increase or maintain their recruiting activities over the first two months of their involvement in the trial and given the demands of the clinical settings, all practices will be encouraged to complete recruitment for the trial within three months of their enrollment and training. Our previous work supports anticipated success of this strategy.

### Timing of Recruitment

A key design feature of this trial is that the allocation of practices within the research network will be carried out prior to the recruitment of the required number of patients. This will be done to ensure proper understanding of the trial and review recruitment strategies to avoid selection bias utilized by our group in a previous randomized controlled cluster design of physical exercise prescription in primary care [45]. Similar differences in patient characteristics at baseline between the SNAC and the control group in this trial allow for valid interpretation of results. We do not anticipate a difference in recruitment times between the two groups because both groups will be counseled regarding recruitment strategies for the trial at the same time. This may be in contrast to other studies where slow uptake of control practices have been reported should the treatment allocation be known prior to recruitment. Hence, practices would potentially see little gain from their participation. Further, unequal timeframes for recruitment of patients to the intervention or control groups could bias comparison. For example, there is good evidence for seasonal variation on the lifestyle factors of physical activity and diet. If either of the groups recruited more patients during a particular season or it was stratified to do so, then they could be expected to have a change in one of the lifestyle interventions regardless of the intervention itself.

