### Study Population

Primary care practices will be recruited using a family practice research network. Randomization to intervention or usual care control will be done by a random number table. Recruitment of patients within the practices will include two successful strategies previously utilized by our group including opportunistic recruitment of consecutive patients during the course of routine, prescheduled, clinic visits or query of the network database for inclusion criteria and screening of patient visit lists [19,37]. All practices will target 10-12 patients each over a 6-month period.

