### Recruitment of Patients

It will be the responsibility of each participating practice and not the research coordinating centre staff to recruit consecutively attending patients with high normal blood pressure and/or impaired glucose tolerance within the selection criteria. Any member of the primary care team can recruit patients. It is anticipated the process would be completed within 2-3 months of enrolment into the program. Delay in recruitment of some practices, due to unforeseen changes in the practice environment including staff leave, vacations, and competing interest in other clinical trials, will be minimized given the established activity of the research network. For example, once a practice has recruited its quota of patients, the strategy used to achieve this quota will be shared with those in the same intervention group by the research staff. No incentives will be utilized as this will not be the case in usual practice. It is apparent that some patients, given the nature of the intervention and assessments, will drop out before the baseline data collection. If this recurs, every effort will be made to replace the patient prior to the randomization. In addition, there is a possibility that some patients will have an exacerbation of their blood pressure or blood glucose through the randomization phase requiring other forms of treatment. This will be treated as an exclusion for the study and patients will be withdrawn. This will not lead to a bias in comparison to the intervention and control arms as both groups will be subjected to the same risk. Whether this could influence the generalizability of the intervention and control situations to general practices is also not an issue as many patients with high normal blood pressure or impaired glucose tolerance will convert to hypertension or T2D at any point in time. Record of those who are withdrawn from the protocol at any point will be analyzed to identify other aspects of prevalence of these conditions and determinants of adherence within the family practice settings.

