The first issue identified during pilot work was that of potential contamination. Although general practitioners tend to "nest" within practices, many other health professionals and staff may move through multiple practices. This was not the case within the current research network; however, this could be an area of concern for wider intervention dissemination. If this potential contamination is ignored however this could lead to dilution of estimates of intervention effect. A second issue stems from the potential slow recruitment of patients in some clusters. While recruitment rates in this trial and previous trials in our experience have been quite good and given that recruitment has to occur prior to randomization in order to prevent bias within individual patients as opposed to practice, this could lead to a lack of incentive among some patients for participation. Further, the resulting delay between recruitment and allocation times allow for patient withdrawals and for conversion of patients to hypertension and T2D which may affect comparability among subjects. Patient withdrawal prior to allocation to intervention however will not bias results, but sample size estimates may need to be inflated to take into account the number of patients recruited who are not eligible at randomization either due to conversion to the clinical syndrome or due to simple withdrawal. Early patient recruitment has several advantages as well as several disadvantages. The large number of patients involved may be a limit to the accommodation of patients involved in clinical trials within the constraints of general practice. However, given that the current study only required 10 patients per practice, this is a relatively small-added time burden to the recruited practices and was not a key concern. It is not our experience that cluster randomized trials in primary care require any additional time or financial support as compared to single centre randomized controlled trials. In fact, since these studies tend to reflect the usual care within practice, cluster randomization seems to ideal to allowing all patients and physicians to engage in the same level of care without discrimination or necessarily added time/resource burden.

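### The protocol gives two opposite orders for practice allocation and patient recruitment; under the allocation-first order, the arm is not concealed from the practice staff who recruit.

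*Protocol article*

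**What the plan says.** All places are in the protocol article.

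**Allocation first.** Timing of Recruitment presents it as a central design feature that "allocation of practices within the research network will be carried out prior to the recruitment of the required number of patients". The stated purpose is to review recruitment strategy and avoid selection bias. Randomization gives each arm its own training: SNAC training, or a sham session on hypertension guidelines of equal length. Timing of the Intervention counts the recruitment period from enrolment and training.

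**Recruitment first.** Methodological Considerations & Limitations reasons from the opposite order: "given that recruitment has to occur prior to randomization in order to prevent bias within individual patients as opposed to practice". It then says that "the resulting delay between recruitment and allocation times allow for patient withdrawals". Recruitment of Patients says that, for patients lost before baseline, "every effort will be made to replace the patient prior to the randomization". Table 1 puts consent at screening and randomization at baseline.

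**Who recruits, and how.** Recruitment of Patients makes each practice, not the coordinating centre, responsible for recruiting consecutive attenders, and adds: "Any member of the primary care team can recruit patients". Study Population allows two routes: opportunistic recruitment of consecutive patients at scheduled visits, or "query of the network database for inclusion criteria and screening of patient visit lists". Once a practice fills its quota, "the strategy used to achieve this quota will be shared with those in the same intervention group by the research staff".

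**Blinding.** Blinding, Treatment allocations and Outcome Assessment cover laboratory staff, assessors and patients. None mentions the practice staff who recruit.

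**The concern.** In a cluster trial, randomizing practices balances practices in expectation. It does not balance patients who are chosen after the practice's arm is known. If recruiters in one arm lean towards patients they expect to change their habits, the arms differ in prognosis from the start. The primary outcomes here, such as blood pressure, fasting glucose, fitness and BMI, plausibly depend on that readiness to change.

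The article recognises the hazard, because one section says that recruitment must come first to prevent bias, yet another section fixes the reverse. A practice or coordinator following the text cannot tell which order applies. Some reassurances also depend on the order. The statement that withdrawals before allocation do not bias the comparison covers few or no patients if practices are allocated before anyone is recruited.

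**Working it through.** No sample size, power or alpha figure is at issue, so there is none to reproduce. The check is a comparison of passages, followed by an illustration of scale.

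**1. Can the two orders be reconciled?** The qualifier in Methodological Considerations contrasts individual patients with practices. The practice is the only randomized unit (Methods/Design; Randomization), so there is no separate patient-level randomization to which the recruitment-first statement could apply. The conflict stands.

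**2. Is the arm concealed from recruiters under allocation first?**
- SNAC practices are trained to deliver SNAC, then recruit. They know their arm in effect.
- Control practices attend a sham session. Partial masking is possible but is not stated.

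**3. Is there room for judgement?** The consecutive rule and measured blood pressure and glucose limit it. It remains in the choice between two routes, in the requirement that patients be willing to take part, and in the exclusion for problems expected to impair compliance (Content of intervention). The last two bear directly on motivation.

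**4. Do recruitment methods stay alike across arms?** Both arms are counselled together at the start (Timing of Recruitment), and all practices receive support (Timing of the Intervention). Later sharing of successful strategies is described only within the same arm, and recruiting activity is not matched between practices. Methods can therefore drift apart.

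**5. Does the analysis repair it?** Intention to treat keeps patients in the arm in which they were enrolled; it does not change who was enrolled. ANCOVA is planned only if a group difference in a potential confounder is observed (data analysis text under Sample Size), so it depends on the imbalance being measured and noticed.

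**6. Illustration of scale.** The shift b is assumed; the documents give none.
- Inputs from Sample Size: SD of systolic change 5.32 to 5.92 mmHg; ICC 0.025; about 90 patients per arm, described as 10 practices of about 10, so n = 90 to 100.
- Design factor = 1 + 0.025 × (10 − 1) = 1.225. The article prints 1.05 for this expression; that is a separate matter, and 1.225 is used here.
- SE = SD × √(2 × 1.225 / n). Smallest: 5.32 × √(2.45/100) = 0.833 mmHg. Largest: 5.92 × √(2.45/90) = 0.977 mmHg.
- With no true effect, the two-sided 5% rejection rate is Φ(b/SE − 1.96) + Φ(−b/SE − 1.96).

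| Assumed shift b (mmHg) | Rate at SE 0.977 | Rate at SE 0.833 |
|---|---|---|
| 0 | 0.050 | 0.050 |
| 0.5 | 0.081 | 0.092 |
| 1 | 0.176 | 0.225 |
| 2 | 0.535 | 0.671 |

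For comparison, take 20% drop-out from 100 (80 retained per arm, 8 per practice). The factor is 1 + 0.025 × 7 = 1.175. With 18 degrees of freedom, the difference detectable at 90% power is (2.101 + 1.330) × SD × √(2 × 1.175/80) = 3.13 to 3.48 mmHg. An assumed shift of 1 to 2 mmHg would be 29% (1/3.48) to 64% (2/3.13) of that.

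**The case against.** The protections are real. Both arms are told to recruit consecutive patients, eligibility rests largely on measured values, the two training sessions are matched for duration, and initial recruitment counselling goes to both arms at once. Stage of change and self-efficacy are among the behavioural measures, which Table 1 schedules at baseline, so proxies for motivation will exist for adjustment. These points lower the risk. They do not conceal the arm, and counselling both arms at the same time deals with the timing of recruitment rather than with who is selected.

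Several stronger readings are tempting, and the documents do not support them:
- *Every practice knows its arm.* This is a safe inference for SNAC practices only; the sham session leaves it open for controls.
- *Recruitment tactics are shared only within an arm.* That describes the later sharing, which the article offers as an example; the initial counselling is joint.
- *Replacing patients before randomization is impossible.* The sentence concerns drop-out before baseline data collection, and Table 1 marks randomization at that visit, so it may loosely mean replacement before the visit. The term is unclear, but the step is possible.
- *The no-bias reassurances are void.* They remain reasonable for withdrawals that truly precede allocation; they do not extend to later ones.
- *Recruiting and baseline-assessing everyone first is the obvious cure.* Methodological Considerations lists its costs: withdrawals, conversion to hypertension or diabetes, weaker incentive and possible inflation of the sample size. Treatment allocations also wants each stage within one week of the previous one.

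**Conclusion.** The contradiction on the order of allocation and recruitment is certain from the text and must be resolved. Under the allocation-first order, a risk of differential patient selection remains that intention to treat does not address and that conditional ANCOVA may address only in part.

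That conclusion assumes that SNAC training effectively reveals the arm and that recruiters keep some discretion despite the consecutive rule. It does not assume that control practices know their arm, or that biased selection will occur. Its size is unknown. The figures of about 8-9%, 18-23% and 54-67% false positives for shifts of 0.5, 1 and 2 mmHg show only how sensitive the comparison would be. A larger sample would not remove such a bias, and it cannot be undone after enrolment.

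**What to change.** 1. Bring Timing of Recruitment, Recruitment of Patients, Methodological Considerations & Limitations and Table 1 to one stated order, and say what the randomization mark at baseline means for a patient whose practice is the randomized unit.
2. Before a practice's arm is disclosed and arm-specific training is given, run the network query and visit-list screen already planned in Study Population, and fix an ordered list of potentially eligible patients. Approach them in that order, and log approaches, refusals and exclusions by arm.
3. Change Recruitment of Patients so that successful recruitment strategies go to practices in both arms.
4. Limit the statement that withdrawal does not bias results to withdrawals that truly precede allocation.

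**Cost.** A short delay before training, some extra logging, and less freedom for opportunistic recruitment. Sharing tactics across arms should cost almost nothing.

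Consenting and baseline-assessing the full quota before disclosure is an optional, stronger step. Early recruits could wait through a recruitment period put at two to three months in one section and six months in Study Population, with the withdrawal and conversion costs that the article itself lists.

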### Recruitment of Practices

This trial was designed to include practices in Southwestern Ontario, which has a higher burden of cardiovascular disease than other parts of the province [44]. We have aimed to recruit a total of 20 practices to the trial with stratification for urban, rural, and academic practice affiliation distribution. We then would obtain a representative balance of practice settings within the region.

### Recruitment of Patients

It will be the responsibility of each participating practice and not the research coordinating centre staff to recruit consecutively attending patients with high normal blood pressure and/or impaired glucose tolerance within the selection criteria. Any member of the primary care team can recruit patients. It is anticipated the process would be completed within 2-3 months of enrolment into the program. Delay in recruitment of some practices, due to unforeseen changes in the practice environment including staff leave, vacations, and competing interest in other clinical trials, will be minimized given the established activity of the research network. For example, once a practice has recruited its quota of patients, the strategy used to achieve this quota will be shared with those in the same intervention group by the research staff. No incentives will be utilized as this will not be the case in usual practice. It is apparent that some patients, given the nature of the intervention and assessments, will drop out before the baseline data collection. If this recurs, every effort will be made to replace the patient prior to the randomization. In addition, there is a possibility that some patients will have an exacerbation of their blood pressure or blood glucose through the randomization phase requiring other forms of treatment. This will be treated as an exclusion for the study and patients will be withdrawn. This will not lead to a bias in comparison to the intervention and control arms as both groups will be subjected to the same risk. Whether this could influence the generalizability of the intervention and control situations to general practices is also not an issue as many patients with high normal blood pressure or impaired glucose tolerance will convert to hypertension or T2D at any point in time. Record of those who are withdrawn from the protocol at any point will be analyzed to identify other aspects of prevalence of these conditions and determinants of adherence within the family practice settings.

The non-random selection of practice patients within the study practices could have impact on the generalizability of the results of this trial. However, this is standard in most randomized clinical trials, whereby convention, patients in participating centres are selected systematically rather than randomly. Implementation of the findings of randomized, controlled trials is an important area of research by our group. Importantly, practices in this trial will be balanced for a practice setting (academic, rural, urban) and will enhance the generalizability of the communities they represent in the future implementation of dissemination strategies.

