**Methods/design:**

The Staged Nutrition and Activity Counseling (SNAC) study is a randomized clustered design clinical trial that will investigate the effectiveness and efficacy of a multi-component lifestyle intervention on cardiovascular disease risk factors and vascular function in patients at risk in primary care. Patients will be randomized by practice to either a standard of care lifestyle intervention or a behaviourally-based, matched prescriptive physical activity and diet change program. The primary goal is to increase physical activity and improve dietary intake according to Canada's Guides to Physical Activity Healthy Eating over 24 months. The primary intention to treat analysis will compare behavioral, physiological and metabolic outcomes at 6, 12 and 24 months post-randomization including estimation of incident hypertension and/or diabetes.

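### The withdrawal rule for patients whose blood pressure or glucose worsens has no defined time window; if it runs past baseline, its equal-risk defence fails and it conflicts with the intention-to-treat analysis

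*Protocol article*

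**What the plan says.** Under Recruitment of Patients, the article expects that "some patients will have an exacerbation of their blood pressure or blood glucose through the randomization phase requiring other forms of treatment". It continues: "This will be treated as an exclusion for the study and patients will be withdrawn". The defence follows at once: "This will not lead to a bias in comparison to the intervention and control arms as both groups will be subjected to the same risk". The same paragraph remarks that many such patients "will convert to hypertension or T2D at any point in time", and says of withdrawn patients: "Record of those who are withdrawn from the protocol at any point will be analyzed to identify other aspects of prevalence of these conditions". It does not say whether those records enter the comparison of the arms.

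The Abstract (Methods/design) sets the analysis: "The primary intention to treat analysis will compare behavioral, physiological and metabolic outcomes at 6, 12 and 24 months post-randomization". New disease is made part of that same analysis, in the words "including estimation of incident hypertension and/or diabetes". Primary Outcome Measures lists clinic blood pressure and fasting glucose; incident disease is not in that list.

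On the order of events, Timing of Recruitment says that "allocation of practices within the research network will be carried out prior to the recruitment of the required number of patients" and calls this a key design feature. Methodological Considerations & Limitations says the reverse, that recruitment has to come before randomization. It places conversions in the gap between the two and limits its no-bias statement to withdrawals before allocation.

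**The concern.** The withdrawal trigger is a rise in the variables that the trial measures as primary outcomes. Once the programme has started, it is supposed to make that rise less frequent in the SNAC arm. Equal risk is then the null hypothesis and cannot be assumed as a safeguard. If converters leave during follow-up, more controls than SNAC patients are lost, those lost are the ones with the highest values, and the events needed for the incidence estimate go with them.

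At entry the concern is different. If practices already know their arm when they recruit, whether a patient counts as needing other treatment is a judgement that can differ by arm even when the patients do not. Under Randomization, the SNAC practices attend programme training and the control practices a hypertension-guidelines session.

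**Working it through.** The article gives no expected number of withdrawals, so there is no stated figure to reproduce. The check has three steps.

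**1. When can the rule act?**

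- *Before practice allocation.* Harmless to the comparison, as Methodological Considerations says. This period exists for patients only if recruitment precedes randomization, which Timing of Recruitment contradicts.
- *After practice allocation, before the baseline visit.* Patients have not yet received the programme, so their underlying risk should be similar. The practices, however, are allocated and trained, and they do the recruiting.
- *After the baseline visit.* The section Randomization says the programme is prescribed at that visit, and Table 1 also marks randomization there. From then on the risks are equal only if the programme has no effect.

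**2. How many would convert?**

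Input: 37% of people with high-normal blood pressure progress to hypertension over four years (Rationale for our intervention). Assumption, not in the article: constant hazard.

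h = −ln(1 − 0.37)/4 = 0.4620/4 = 0.1155 per year; P(t) = 1 − exp(−h·t).

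| Window | Basis in the article | P(t) |
|---|---|---|
| 1 week | target gap between stages (Treatment allocations, Timing) | 0.2% |
| 3 months | recruitment period (Timing of the Intervention) | 2.8% |
| 12 months | analysis time point | 10.9% |
| 24 months | analysis time point | 20.6% |

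Study Population allows six months for recruitment; the same formula then gives 5.6%.

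With about 90 patients per arm (Sample Size), 24 months gives 90 × 0.206 = about 18.6 control conversions if all had high-normal blood pressure. For assumed risk ratios of 0.5 to 0.8, the SNAC arm would have 9.3 to 14.9.

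**3. What would withdrawal during follow-up do to the systolic difference?**

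From the article: entry systolic pressure 130–139 mmHg (Content of intervention) and SD of change 5.32 to 5.92 mmHg (Sample Size). Assumed: entry values uniform on 130–140, mean change of zero in controls, true effects of 0 to −5 mmHg, and removal of anyone at 140 or above at follow-up. Simulation with 2 million patients per arm:

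| SD | True effect | Removed, control | Removed, SNAC | Effect among those kept | Shrinkage |
|---|---|---|---|---|---|
| 5.32 | 0 | 20.7% | 20.6% | −0.01 | none |
| 5.32 | −2 | 20.7% | 12.5% | −1.43 | 28% |
| 5.32 | −3 | 20.7% | 9.4% | −2.19 | 27% |
| 5.32 | −5 | 20.6% | 4.9% | −3.84 | 23% |
| 5.92 | 0 | 22.5% | 22.5% | 0.00 | none |
| 5.92 | −2 | 22.5% | 14.5% | −1.37 | 32% |
| 5.92 | −3 | 22.5% | 11.3% | −2.10 | 30% |
| 5.92 | −5 | 22.5% | 6.5% | −3.68 | 26% |

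Losses are equal, and the estimate undisturbed, only in the rows with no true effect. The 140 cut-off stands in for the article's actual trigger, a need for other treatment, which one reading would not establish. The shrinkage is therefore an illustration.

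**The case against.** The best reply is that the rule concerns entry only. It sits under recruitment, directly after a passage on drop-out before baseline and replacement before randomization. It is qualified by the randomization phase and by a need for other treatment. Table 1 marks randomization at the baseline visit, stages are meant to follow each other within a week, and Methodological Considerations places conversion between recruitment and allocation. The remark on conversion at any time belongs to an argument about generalizability and does not set a withdrawal window. Records of withdrawn patients are to be analysed, so loss of the events is not certain.

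Most of this stands. A reader might infer that everyone who converts over 24 months is removed, that about a fifth of controls and the outcome itself are lost, and that the arms are therefore biased. The article does not say that. A reader might also assume wider spreads, SD 6 to 10 mmHg, and arrive at shrinkage of 35% to 47%; the article's own SDs and entry range do not support so large a figure. Nor does the 37% apply to the whole arm, since patients with impaired glucose tolerance are also enrolled.

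The reply does not remove the problem. The phase is undefined. The no-bias statement for withdrawal before allocation cannot apply to patients in a design that allocates practices first. Pre-baseline drop-outs are handled separately from converters, for whom no replacement is mentioned. The equal-risk sentence itself carries no time limit.

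**Conclusion.** The point holds conditionally. Two things are established from the text alone: the withdrawal window is undefined, and the article contradicts itself on whether allocation or recruitment comes first. If practices are allocated first, every withdrawal under this rule follows allocation.

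Bias is not established; it depends on how far the rule reaches. If it covers entry only, about 0.2% to 2.8% of high-normal blood pressure patients would convert, little or none of the 6- to 24-month outcome is lost, and the remaining concern is selective exclusion by practices that know their arm. If it covers follow-up, about 10.9% of high-normal blood pressure controls would convert by 12 months and 20.6% by 24 months, and the illustrative systolic effect shrinks by about 23% to 32% towards zero. On that reading the rule conflicts with the intention-to-treat analysis of blood pressure and glucose, and with the incidence estimate promised in the Abstract. The conversion figures rest on a constant hazard, the shrinkage on the assumptions listed with the simulation. The article gives no corresponding rate for glucose.

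**What to change.** - Define the randomization phase as ending at the baseline visit. Limit the exclusion to patients found ineligible before that visit, and report their number by arm. The exclusion should not be dropped for these patients, because the entry criteria rule them out.
- Reconcile Timing of Recruitment, Recruitment of Patients, and Methodological Considerations & Limitations on the order of allocation and recruitment.
- State that patients who convert or start other treatment after baseline stay in scheduled outcome measurement, are analysed by allocated practice, and are counted as incident cases.
- Delete the equal-risk sentence.

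How values after added medication are handled in the main analysis can be left to the SAP. Treatment decisions are unaffected; only measurement and the analysis set change. The cost is some protocol wording and keeping already scheduled visits for converters.
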